### Sample Size

#### Randomized Controlled Medication Adherence Study

We assumed that the mean longitudinal adherence will remain stable at 95% in the intervention group during the follow-up period, whereas it would decrease from 95% to 80% in the control group during the 340 days from randomization to the end of follow-up. We also assumed an SD for the logit of longitudinal adherence of 1.8, for both groups and at all timepoints. This corresponds to 95% individual adherence in the intervals 10%-99.3% and 35%-99.9% in the control and intervention groups, respectively, at the end of follow-up. A sample size calculation was performed to simulate individual series of daily medication (1=at least the correct number of daily openings of the electronic monitor; 0=fewer daily openings than prescribed) according to the above parameters to consider both the interindividual variability (SD 1.8) and the intraindividual variability (the measurement error). Considering that the number of measures of a subject will be 340 and assuming a 10% dropout in the middle of the year, 120 patients must be included in the study (60 in each group) to reach a power of 80% with a .05 significance level when comparing the mean of the logit of global adherence between groups using a two-tailed Student *t* test. Differences are considered statistically significant if *P*<.05.

#### Pharmacokinetic and Pharmacodynamic Study

It has been empirically determined that at least 50 patients with several samples per PKI are necessary to characterize drug pharmacokinetics and variability.

### Collection and Management of Data

In collaboration with the investigators, the community pharmacy of Unisanté will manage the PKI adherence data, and the Center of Experimental Therapeutics will manage the blood samples as well as the clinical, biological, and sociodemographic data. The schedule of enrollment, intervention, and assessments is shown in Multimedia Appendix 3. Sociodemographic and relevant clinical and biological information regarding the evaluation of the disease will be obtained from the administrative and electronic patient medical records (Soarian, Cerner). The data will be registered prospectively in the REDCap (Research Electronic Data Capture; Vanderbilt University) platform, a secure web application for research data collection, providing a unique study identification number for each patient. To ensure confidentiality and data quality, only principal investigators will have access to this file. After the analysis, the database will be registered in the secured data repository of the University of Geneva (Yareta). Patient blood samples will be stored in the Center of Experimental Therapeutics, and the health data will be stored in the data warehouse of the CHUV for a maximum of 15 years after the end of the study before destruction.

### Data Analyses

#### Medication Adherence Analysis

Adherence to PKI will be assessed using electronic monitor, calculated pill counts, and patient reports. Medication behavior will be described with a binary variable (1=at least the correct number of daily openings of the electronic monitor; 0=fewer daily openings than prescribed) in each group. This coding method is commonly used; however, this code cannot discriminate overadherence, which is considered in the same way as optimal adherence. The implementation will be described in each group using generalized estimating equation models; persistence with PKI (ie, adherence until PKI discontinuation) will be represented using a Kaplan-Meier survival curve [14]. Global adherence will be estimated in each group with the proportion of patients with correct medication taking, defined as ≥95% days with correct dosing during days 1 to 360, compared between groups using a chi-square test. As ≥95% days with the correct dosing threshold is an assumption, we will perform sensitivity analysis with other thresholds such as 90%, 85%, and 80%. Multivariate logistic regression models will be used to evaluate whether any detected effect of the intervention remained after adjusting for potential sociodemographic or clinical confounders. As a secondary analysis, the difference in medication taking will be explored across genders.

A systematic computerized term search in the adherence reports of the intervention group will be performed to identify the most frequent variables affecting PKI adherence, and a regression model will be used to discover their association with adherence [35].

Sociodemographic data and quality of life and beliefs about medication of patients who refused to participate and completed both questionnaires versus those who accepted to participate in the adherence study will be compared at baseline. For patients included in the adherence study, the results of the questionnaires will be compared at randomization, 6 months, and at the end of the study. Changes in *Belief about Medicines Questionnaire* and *European Organization for Research and Treatment of Cancer Quality of Life Questionnaire* or the *Treatment Satisfaction with Medicines Questionnaire* will be described longitudinally for the included patients and transversely per group at 6 and 12 months. Medians and IQRs or proportions will be used as appropriate. Nonparametric tests (eg, Mann-Whitney-Wilcoxon) or Fisher exact test of two proportions will be used to test the differences between groups.

Ultimately, the adherence patterns and their relationship with drug exposure and clinical response will be evaluated in an exploratory analysis.

To minimize interpretation bias, the statistician will not be aware of the group assignments during the analysis. The data will be analyzed in an intention-to-treat manner. All statistical analyses will be performed using the R statistical package (version 3.6, The R Foundation for Statistical Computing) [36].

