### Outcomes

#### Primary Outcomes: Randomized Controlled Medication Adherence Study

The primary outcome was global adherence, defined as the percentage of days with correct medication use of each subject. The sample size was calculated to ensure sufficient power to test the difference in the mean logit global adherence between groups (see the *Sample Size* section). Medication adherence will also be compared between groups following the three operational definitions defined by the EMERGE (European Society for Patient Adherence, Compliance, and Persistence Medication Adherence Reporting Guideline) guidelines: implementation of treatment during the persistent period (daily management of oral targeted anticancer drugs), persistence with treatment (the distribution of times between enrollment and discontinuation), and longitudinal adherence (the product of persistence and implementation) [14,28,29].

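### Global adherence, the primary outcome, is sized as a continuous percentage with a t test but analysed as a 95% responder proportion with a chi-square test, which has about 63% power instead of 80%

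*Protocol article*

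**What the plan says.** Three places in the protocol article deal with global adherence.

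- **Outcomes (Primary Outcomes: Randomized Controlled Medication Adherence Study).** This section defines the measure per patient: "The primary outcome was global adherence, defined as the percentage of days with correct medication use of each subject". The next sentence ties the sample size to it: "The sample size was calculated to ensure sufficient power to test the difference in the mean logit global adherence between groups".
- **Sample Size (Randomized Controlled Medication Adherence Study).** 120 patients, 60 per group, give 80% power at the .05 level "when comparing the mean of the logit of global adherence between groups using a two-tailed Student" t test. The inputs are "We assumed that the mean longitudinal adherence will remain stable at 95% in the intervention group during the follow-up period", while "it would decrease from 95% to 80% in the control group during the 340 days from randomization to the end of follow-up", and an SD of 1.8 on the logit scale.
- **Data Analyses (Medication Adherence Analysis).** "Global adherence will be estimated in each group with the proportion of patients with correct medication taking, defined as ≥95% days with correct dosing". The groups are compared by chi-square test over days 1 to 360. The section concedes that the 95% threshold is an assumption and offers 90%, 85% and 80% as sensitivity cut-offs. Adjustment is by logistic regression.

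The analysis section contains no t test and no other between-group test of the per-patient percentage. The generalized estimating equation models named there describe implementation, a separate measure confined to the persistent period.

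**The concern.** One named outcome has two definitions and two tests, and the sample size supports only one of the pairs.

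- **Different questions.** The first pair asks whether mean adherence differs, on the logit scale. The second asks whether the share of patients above a cut-off differs.
- **Lost power.** Dichotomizing a continuous measure discards information. If the analysis section is followed, the stated 80% power does not apply to the test that is run.
- **Open choice.** The two tests can give opposite answers on the same data. With both in the text and neither analysis tied to the word primary in the analysis section, the headline result could be chosen after both are known.

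**Working it through.** **Inputs, from the Sample Size section.** Intervention 95% throughout; control 95% falling to 80%; 340 daily measures; logit SD 1.8; 10% dropout at mid-year; 60 per group; two-sided .05. The shape of the control decline is not given. I take it as linear in percentage points and test that choice below.

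**Step 1: which scale the 95% and 80% are on.** The section gives the ranges that should contain 95% of patients at the end of follow-up: "This corresponds to 95% individual adherence in the intervals 10%-99.3% and 35%-99.9% in the control and intervention groups, respectively". Using logit(p) ± 1.96 × 1.8:

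- control: logit(0.80) = 1.386, giving 10.5% to 99.3%;
- intervention: logit(0.95) = 2.944, giving 35.8% to 99.8%.

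These match to rounding, so 95% and 80% are back-transformed logit means.

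**Step 2: reproduce the stated 80%.** Each patient has an effect drawn from N(0, 1.8²) on the logit and a daily 0/1 series of 340 days, or 170 days for the 10% who drop out. The patient's summary is ln[(s + 0.5)/(N − s + 0.5)], where s is correct days out of N. The difference in group means is 0.913 and the SD about 1.764. The normal approximation is

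Φ(0.913 / (1.764 × √(2/60)) − 1.96) = Φ(2.835 − 1.96) = Φ(0.875) = 0.81.

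Simulation of the t test (40,000 trials) gives 80.0%. The plan's figure is reproduced.

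**Step 3: the chi-square test on the same model.** The probability of at least 95% correct days, averaged over the patient effect and the dropout mix, is p₁ = 0.5061 (intervention) and p₂ = 0.3026 (control), so the difference is 0.2035 and p̄ = 0.40435.

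- √(2p̄(1 − p̄)) = √0.4817 = 0.6940
- √(p₁(1 − p₁) + p₂(1 − p₂)) = √0.4610 = 0.6790
- Power at 60 per group: Φ[(0.2035 × √60 − 1.96 × 0.6940)/0.6790] = Φ[(1.576 − 1.360)/0.6790] = Φ(0.318) = 0.62
- Full enumeration of the two binomials gives 63%, or 56% with continuity correction.
- Size for 80% power: (1.96 × 0.6940 + 0.8416 × 0.6790)² / 0.2035² = 1.932² / 0.0414 ≈ 90 per group

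**Step 4: the other cut-offs (60 per group, no continuity correction).**

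| Cut-off | Responders, intervention v control | Chi-square power |
|---|---|---|
| 95% | 51% v 30% | 63% |
| 90% | 66% v 46% | 64% |
| 85% | 75% v 56% | 61% |
| 80% | 81% v 63% | 57% |

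None recovers the loss.

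**Step 5: disagreement.** At 60 per group the tests reached different significance verdicts in 22% of simulated trials: t test only in 19%, chi-square only in 3%.

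**Step 6: sensitivity.**

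| Variation | t test | Chi-square at 95% |
|---|---|---|
| Base case | 80% | 63% |
| Decline linear on the logit scale | 66% | 50% |
| 65 per group | 84% | 67% |
| 21 baseline days counted in the window | 74% | 57% |

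The third row uses the 130 patients reported in Results, if all were randomized in equal numbers, which the article does not state. The fourth arises because the sample size uses 340 days after randomization while the analysis section uses days 1 to 360 without saying whether the baseline period of at least 21 days is included.

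**The case against.** The best reply is that the primary test is already stated twice, in the Outcomes and Sample Size sections, and that the analysis section never calls the chi-square comparison primary. On that reading the t test was left out of one section and the label was reused for a responder summary; a percentage and its dichotomy can both be reported. This is a fair account of how the text may have arisen, and it shows which version to keep. It does not remove the contradiction: the analysis section gives the primary outcome's name to a different quantity and attaches a test, threshold sensitivity analyses and an adjusted model to it.

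The plan also keeps the statistician unaware of group assignment and analyses by intention to treat. That helps, but it does not settle which of two results becomes the headline once the groups are identified.

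The power figure rests on a decline shape that the plan does not state. This stands, and the figure should carry that condition. The logit-linear path does not reproduce the stated 80%, and it leaves a gap of similar size (66% v 50%).

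Reading 95% and 80% as true mean percentages would lift the chi-square test to about 84-86%. The t test would then have 96%, not 80%, and the plan's own ranges in Step 1 rule that reading out.

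The required size is sensitive to small changes in the responder proportions: simulations put it between 89 and 96 per group. Every value in that range is well above 60.

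**Conclusion.** Wrong as written, and it must be corrected because it concerns the definition and test of the primary outcome. The 80% power belongs to the t test on logit global adherence. The chi-square test that the analysis section specifies has about 63% (61-66% across simulations and dropout handling; roughly 53-59% with continuity correction). It would need about 90 per group for 80%.

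These figures assume a control decline linear in percentage points, the logit-normal model of the Sample Size section, and dropouts who contribute their first 170 days. The contradiction itself depends on none of these assumptions.

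**What to change.** In Medication Adherence Analysis, state that the primary analysis is the two-sided between-group comparison of the mean logit of each patient's percentage of correct days, as in the Outcomes and Sample Size sections. Say how 0% and 100% are handled before the logit is taken. Use one observation window throughout, and say whether baseline days count. Label the proportion with at least 95% correct days, its 90%, 85% and 80% variants and the logistic models as secondary, under a name other than global adherence.

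The alternative, re-sizing for the binary outcome, is not practical: recruitment to the adherence part ended in March 2021 with 130 patients, against about 180 needed (2 × 90).

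The cost is one paragraph of wording. No data or patients are added, and the responder proportion is still reported. The change should be dated and made before any group-level result is seen.

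### The 80% power belongs to a t test on logit percentage of correct days, but the analysis section redefines global adherence as a ≥95% responder proportion tested by chi-square, with about 62–63% power under the same assumptions

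*Protocol article*

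**What the plan says.** Three places in the protocol article bear on the primary comparison.

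- **Outcomes, Primary Outcomes:** "The primary outcome was global adherence, defined as the percentage of days with correct medication use of each subject". The same paragraph says the sample size was set to give "sufficient power to test the difference in the mean logit global adherence between groups".
- **Sample Size, Randomized Controlled Medication Adherence Study:** 120 patients, 60 per group, give 80% power at the .05 level when "comparing the mean of the logit of global adherence between groups" with a two-tailed Student t test, on 340 daily measures per patient and 10% dropout at mid-year.
- **Data Analyses, Medication Adherence Analysis:** global adherence becomes a responder proportion, "defined as ≥95% days with correct dosing during days 1 to 360, compared between groups using a chi-square test". The 95% threshold is called an assumption, and 90%, 85% and 80% are listed as sensitivity analyses. Logistic regression is then planned to see whether a detected intervention effect survives adjustment.

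The t test on the logit appears nowhere under Data Analyses, and no power is given for the chi-square.

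**The concern.** The same named outcome is continuous in two sections and binary in the third, with a different test for each. A statistician working from Data Analyses would run the chi-square as the test of the primary outcome, and the adjusted logistic models that follow build on the binary version. The stated 80% was not calculated for that test, and dichotomising a continuous score normally costs power. A null result could then reflect the choice of test rather than the intervention. With two tests that could each be called primary, a positive result could also be chosen once both P values are known.

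**Working it through.** **Inputs (Sample Size section).** Intervention: "We assumed that the mean longitudinal adherence will remain stable at 95% in the intervention group during the follow-up period". Control: "it would decrease from 95% to 80% in the control group during the 340 days from randomization to the end of follow-up". Spread: "We also assumed an SD for the logit of longitudinal adherence of 1.8, for both groups and at all timepoints". Also 340 days, 10% dropout at mid-year (taken as day 170), 60 per group, two-sided .05.

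**Step 1: the mean and SD agree with the text.** logit(0.95) = 2.944, logit(0.80) = 1.386, and 1.96 × 1.8 = 3.528. Back-transforming 1.386 ± 3.528 gives 10.5%–99.3%. Back-transforming 2.944 ± 3.528 gives 35.8%–99.85%. The protocol states "95% individual adherence in the intervals 10%-99.3% and 35%-99.9% in the control and intervention groups, respectively".

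**Step 2: reproduce the stated 80%.** The shape of the control decline is not given.

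- *Linear on the percentage scale.* The average control logit over follow-up is 2.013, so the difference is 2.944 − 2.013 = 0.931. SE = 1.8 × √(2/60) = 0.3286. Power = Φ(0.931/0.3286 − 1.960) = Φ(0.873) = 80.9%. Required n = 2 × (1.960 + 0.842)² × 1.8² / 0.931² = 50.86/0.867, or 59 per group.
- *Linear on the logit scale.* The difference is (2.944 − 1.386)/2 = 0.779. Required n = 50.86/0.607, or 84 per group; simulated power with 60 is about 66%.

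Simulating daily 0/1 series with the percentage-linear fall, a constant N(0, 1.8) patient effect, dropouts scored on their observed days, and an empirical logit gives 80.6% (2,500 trials) and 81.2% (8,000 trials). The stated 80% is reproduced, and only the percentage-linear fall does so.

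**Step 3: the chi-square on the same simulated data.** About 30.2% of control and 50.6% of intervention patients reach ≥95% correct days.

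- Difference 0.204; pooled proportion 0.404.
- Null SE = √(2 × 0.404 × 0.596/60) = 0.0896.
- Alternative SE = √((0.302 × 0.698 + 0.506 × 0.494)/60) = 0.0876.
- Power = Φ((0.204 − 1.960 × 0.0896)/0.0876) = Φ(0.32) = 62.7%. Simulation gives 63–64%, or 55–56% with continuity correction.
- For 80% power: n = [(1.960 × 0.694 + 0.842 × 0.679)/0.204]² ≈ 90 per group (about 100 with continuity correction). Relative efficiency is 60/90 ≈ 0.67, a loss of about one third.

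With thresholds of 90%, 85% and 80% the chi-square has about 65%, 61% and 59%, so no listed threshold recovers the power.

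**Step 4: vary what the text leaves open (60 per group, ≥95% threshold).**

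| Control decline; other assumption | t test | Chi-square | With continuity correction |
|---|---|---|---|
| Linear in %; dropouts on observed days | 81% | 63% | 55% |
| Linear in %; dropouts excluded | 80% | 62% | 54% |
| Linear in %; days after dropout counted as missed | 71% | 60% | 51% |
| Linear in %; patient effect varying over the year | 85% | 66% | 59% |
| Linear in logit; dropouts on observed days | 65% | 49% | 41% |
| Linear in logit; days after dropout counted as missed | 57% | 47% | 39% |
| Linear in logit; patient effect varying over the year | 72% | 54% | 45% |

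The uncorrected chi-square runs from 47% to 66% and is 10 to 19 points below the t test on the same data.

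**Step 5: 340 days against days 1 to 360.** Monitoring starts at least 21 days before randomization, so days 1 to 360 may include the baseline period. Adding 20 days at 95% in both groups lowers the chi-square to 59% and the t test to 76%.

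**Step 6: choosing between two tests.** With both groups stable at 95%, claiming success if either the t test or the ≥95% chi-square is significant gives about 8–9% false positives, against a nominal 5%.

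**The case against.** The strongest reply is that the primary comparison is already fixed twice, under Outcomes and under Sample Size, with variable, test, N and alpha. Data Analyses never calls the chi-square primary, so it could be a mislabelled responder analysis, and then the 80% stands. That reading is possible, and the protocol does not claim 80% for the chi-square. But Data Analyses attaches the primary outcome's own name to the proportion and omits the t test altogether, so the text does not settle which is meant. This is a stated contradiction, not a detail left to an analysis plan.

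Several stronger readings are tempting but unsupported:

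- *That dichotomising discards most of the information.* 60 against about 90 per group is about one third.
- *That there are five rival primary tests.* The 90%, 85% and 80% thresholds are labelled sensitivity analyses. The rivals are two.
- *That patients with 100% correct days would be lost because their logit is infinite.* The protocol states no such exclusion, and the handling is ordinary analysis-plan detail.
- *That the chi-square's power is exactly 63%.* That value depends on a decline shape, dropout scoring and patient effect that the text does not state.

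The statistician's masking to group is a partial safeguard. It does not prevent choosing a test by its P value, because two-sided P values do not depend on which group carries which label. The 130 patients reported as included help only a little: split equally, 65 per group gives the chi-square about 67%.

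**Conclusion.** The contradiction is explicit and concerns the primary comparison, so it should be resolved before the final analysis. The 80% is sound for the t test on the logit and does not carry over to the chi-square. Under the model that reproduces 80% (control fall linear in percentage, constant patient effect, dropouts scored on observed days), the chi-square has about 62–63% power, or about 55% with continuity correction. The direction and rough size of the loss held in every gradual-decline variant tried. The 47–66% range describes those variants and is not a bound. The chi-square exceeded 80% when control adherence was set at 80% from day 1, which contradicts the stated decline and would give the t test over 99%. The room for selecting a test is real but limited to two tests; nothing in the document suggests that selection is intended.

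**What to change.** In Medication Adherence Analysis, name the between-group two-tailed t test on the logit of each patient's percentage of correct days as the single primary analysis, matching Outcomes and Sample Size. An empirical logit, for example log((y + 0.5)/(n − y + 0.5)) with y correct days out of n, keeps patients with 100% correct days computable. Give the ≥95% proportion its own name, so that global adherence has one meaning, and list it with its chi-square and the 90%, 85% and 80% thresholds as secondary. State one scoring window, reconciling the 340 days after randomization with days 1 to 360, and say whether baseline days count.

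If the chi-square is to be primary instead, redefine the outcome under Outcomes and Sample Size and restate the power with 60 per group as roughly 55–63% under the sizing assumptions.

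The first option needs only wording, made before group assignments are linked to the adherence data. It needs no new data or patients, and its one cost is that the responder proportion becomes secondary.

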### Enrollment of Participants

This translational study will be conducted at the Medical Oncology Service of the Department of Oncology of the Lausanne University Hospital (CHUV) outpatient clinic (Lausanne, Switzerland) in collaboration with the Community Pharmacy of the Center for Primary Care and Public Health Unisanté (Lausanne, Switzerland) and the Center for Research and Innovation in Clinical Pharmacy Sciences (CHUV).

Adult patients aged >18 years who were treated with a PKI for solid tumors and followed at the CHUV were eligible to participate in this study. Participants with an inability to make decisions, with cognitive disorders, under tutelage, or not fluent in French or English or without the aid of an interpreter will be excluded from the study. Patients will be excluded solely from the medication adherence part of the study if they do not self-manage oral anticancer treatment (ie, nursing homes and home care services) or if they are already enrolled in an interventional study. If one PKI is switched to another PKI during the study, the patient will continue to participate in the study. However, if the PKI treatment is stopped or changed to a non-PKI anticancer treatment, the participant exits the OpTAT study; but, the data collected are kept for analysis.

The OpTAT study is voluntary, and patients will need to sign an informed consent form to participate in the medication adherence study, the pharmacokinetic and pharmacodynamic study, or both. The recruitment of participants began in May 2015. It ended in March 2021 for the medication adherence part but is ongoing until December 2021 for the pharmacokinetics part.

Oncologists were asked to refer eligible patients to a pharmacist PhD student or to the research staff from the Center of Experimental Therapeutics (CHUV), who will present the informed consent form to the patient after the medical visit. The participants will follow their treatment as usual, and no changes in the usual medical procedure will be made. No payment or compensation will be provided to the patients or to the oncologists as the patients are being seen as part of their routine follow-up clinical care.

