### Randomized Controlled Medication Adherence Study

#### Instruments: Use of the Electronic Monitors MEMS and Questionnaires in Both Groups

All patients participating in the medication adherence study will use an electronic monitor (MEMS and MEMS AS, AARDEX Group) for 12 months or until PKI is stopped. The electronic monitor registers the date and time of each opening, and a liquid-crystal display monitor on top of the cap indicates the number of daily openings to the patient. All patients included in the study will be asked to complete two validated questionnaires at three timepoints: inclusion, 6 months postinclusion, and at the end of the study. The first questionnaire is the *Belief about Medicines Questionnaire*, which assesses the patient’s cognitive representation of medication [21]. The second is the *European Organization for Research and Treatment of Cancer Quality of Life Questionnaire* (version 3.0), which assesses the quality of life of patients with cancer [22]. During the initial months of the study implementation, the patients with cancer filled out the *Treatment Satisfaction with Medicines Questionnaire* [23]; however, it was switched to the *European Organization for Research and Treatment of Cancer Quality of Life Questionnaire*, as the latter was more adapted to patients treated with a PKI. The questionnaires were translated and validated in French, with satisfactory psychometric properties [24-26].

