#### Assignment of the Intervention

The collection of adherence data patterns in both groups at baseline is crucial to check whether adherence patterns are homogeneous between the groups before the intervention starts. In both groups, patients will use an electronic monitor for at least 21 days before randomization. At the end of the baseline period, the patients will be randomized 1:1 to either attend the medication adherence program (intervention group) or be part of the standard of care (control group; Figure 1). The randomization lists will stratify participants according to their cancer type and the time elapsed between PKI initiation and the time of inclusion (less or more than 30 days). The randomization sheet lists 1 (intervention group) or 0 (control group) and will be provided by an independent researcher from the Unisanté Research Support Unit. The randomization list established by Excel (version 2016, Microsoft) will be based on variable size block randomization to prevent predictability and ensure a balanced allocation to each group. After randomization, the patient, research team, pharmacy, and clinical team will all be aware of the assigned group.

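### Questionnaire timepoints are named differently for collection and for analysis, and the planned group tests make no adjustment for the inclusion score

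*Protocol article*

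**What the plan says.** On collection, the protocol article (Instruments: Use of the Electronic Monitors MEMS and Questionnaires in Both Groups) asks all patients to "complete two validated questionnaires at three timepoints: inclusion, 6 months postinclusion, and at the end of the study". The same section says that a treatment satisfaction questionnaire was used in the first months and then replaced by the quality-of-life questionnaire.

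On analysis, the Medication Adherence Analysis section states that for patients in the adherence study "the results of the questionnaires will be compared at randomization, 6 months, and at the end of the study". The next sentence says that changes in the beliefs questionnaire, and in the quality-of-life or the satisfaction questionnaire, "will be described longitudinally for the included patients and transversely per group at 6 and 12 months". Differences between groups are then to be tested with nonparametric tests, with Mann-Whitney-Wilcoxon as the example, or with Fisher's exact test. No adjustment for the inclusion score is mentioned.

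Three other statements fix the dates:
- Assignment of the Intervention: "patients will use an electronic monitor for at least 21 days before randomization".
- Instruments section: monitoring runs "for 12 months or until PKI is stopped".
- Enrollment of Participants: "if the PKI treatment is stopped or changed to a non-PKI anticancer treatment, the participant exits the OpTAT study", with the data already collected kept for analysis.

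**The concern.** The text schedules no form at randomization, yet randomization is the first comparison point. The last form has two names, and these mean the same date only for patients who stay on a PKI for the full year. An analyst working from this text would have to decide which form is the baseline, whether 6 months counts from inclusion or from randomization, and what belongs in the 12-month comparison.

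The last decision matters most. The Objectives section hypothesizes that persistence differs by arm, so the number of early stoppers may differ by arm too. The 12-month comparison could then depend on how their forms, if there are any, are classed.

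The second issue is efficiency. Both arms supply a score before randomization on each instrument in use at the time, but the stated between-group tests do not adjust for it. The article plans multivariable adjustment only for adherence.

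**Working it through.** The protocol gives no sample-size or power figure for the questionnaires. Its only such figure for the randomized part, 80% power with 60 per group, concerns global adherence. A simulation of that design gave 79.5% when control adherence falls linearly on the probability scale and 67.7% when it falls linearly on the logit scale. Nothing below depends on it.

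**Timepoints side by side**

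| | First | Middle | Last |
|---|---|---|---|
| Collection | inclusion | 6 months after inclusion | end of the study |
| Analysis, first sentence | randomization | 6 months, origin not stated | end of the study |
| Analysis, second sentence | not named | 6 months | 12 months |

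**Baseline.** The gap between inclusion and randomization is at least 21 days, and no upper limit is given. The inclusion form comes before randomization, so it is a valid baseline. Only its label is wrong.

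**Last form, patients who complete.** Follow-up is specified "during the 340 days from randomization to the end of follow-up" (Sample Size). With the minimum baseline period, 21 + 340 = 361 days from inclusion. For these patients the end of the study and 12 months after inclusion coincide.

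**Last form, early stoppers.** The two labels diverge here. Their number is not known in advance, but the article gives two guides:
- Planned dropout of 10% (Sample Size): 0.10 × 60 = 6 per group, 12 of 120.
- Feasibility persistence of 85% at 12 months (Background): 0.15 × 60 = 9 per group, 18 of 120. That study covered several classes of oral anticancer drug, not only PKIs, so this is a rough guide.

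Dropout in the middle of the 340 days falls at 340 / 2 = 170 days after randomization, or 21 + 170 = 191 days after inclusion. That is close to the 6-month form and about six months short of month 12.

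**Gain from adjusting for the inclusion score.** Let r be the correlation between the inclusion score and the later score, with equal variance σ² at both times. The article gives no value for r; 0.5 to 0.7 is an assumption.
- Raw later score: variance σ².
- Change from inclusion: variance 2(1 − r)σ².
- Adjusted for inclusion score: residual variance (1 − r²)σ².

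| r | Raw | Change | Adjusted | Reduction against raw | Reduction against change |
|---|---|---|---|---|---|
| 0.5 | 1.00σ² | 1.00σ² | 0.75σ² | 25% | 25% |
| 0.7 | 1.00σ² | 0.60σ² | 0.51σ² | 49% | 1 − 0.51/0.60 = 15% |

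The ratio of adjusted to change-score variance is (1 + r)/2, which never exceeds 1. In large samples, adjustment is therefore no less efficient than either alternative. These formulas are for a linear model; for rank-based tests they indicate the likely size only.

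**The case against.** The strongest reply is that this is mostly wording. For completers with the minimum baseline period, the two names for the last form mean the same date. The inclusion form serves as baseline under either label. The assessment schedule is in Multimedia Appendix 3, which is not shown and may settle every date. Visit windows and the handling of exit forms are details that an article commonly leaves to the full protocol or analysis plan. Changes are to be described longitudinally, so the inclusion score is not ignored. The questionnaires are in neither the primary nor the secondary outcomes.

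Much of this stands. It limits the timepoint point to reconciling labels, and the absence of windows is not held against the article. It does not remove the conflict between two sections of the same text. Nor does describing changes supply an adjusted group comparison: whether the tests are run on raw scores or on changes, adjusting for the inclusion score is at least as efficient in large samples.

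A reader might infer more in three places, and the documents do not support it.
- **Exit forms counted as 12-month values.** No section says that an early stopper completes an exit form, or that such a form is assigned to month 12. Such patients may equally be missing at month 12, since the Missing Data section rules out imputation. One can construct a spurious difference: with 30% against 15% early stoppers and exit scores 15 points worse, (0.30 − 0.15) × 15 = 2.25 points in the mean. But the 30% and the 15-point deficit are assumptions, and the exit form itself is undocumented.
- **No usable value before randomization.** The inclusion form is one.
- **Two instruments pooled.** The article joins them with an or because one replaced the other. It does not say that scores are combined or that change is taken across instruments.

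**Conclusion.** The point holds in a limited form. The article names the baseline and final questionnaire timepoints inconsistently, and the passages need to be reconciled. The final labels can differ for early stoppers, about 6 to 9 of 60 per group on the article's own planning figures. Bias from mixing forms is possible but not shown.

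The planned group tests also pass up a nearly free gain in precision. The variance reduction is 25% to 49% against raw scores and 15% to 25% against change scores, if the correlation with the inclusion score is 0.5 to 0.7 and variances are equal over time. A weaker correlation means a smaller gain, in proportion to r² against raw scores. Adjustment does not cure selection: if early stoppers have no 12-month form, that comparison still covers only the patients who supplied one.

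The consequence is confined to the beliefs, quality-of-life and satisfaction analyses. The primary and secondary outcomes, the sample size and the power are untouched.

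**What to change.** In the Medication Adherence Analysis section:
1. Name the inclusion form as the baseline in place of randomization, and count 6 months from inclusion, as the collection section does.
2. Use one definition of the final timepoint that agrees with the collection section.
3. Replace the unadjusted between-group tests at 6 and 12 months with a comparison adjusted for the inclusion score on the same instrument, for example ANCOVA, or a rank-based ANCOVA if scores are skewed.
4. Analyse the quality-of-life and satisfaction questionnaires separately.
5. If exit forms exist, describe them separately or use them only in a sensitivity analysis. Do not adjust for time of completion: persistence may affect it, so it is a post-randomization variable and adjusting for it could itself bias the arm comparison.

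The cost is analysis wording, with no new data collection. The article places the final analysis in 2022 with data collection still in process, so the change can be made beforehand. The downside is that patients without an inclusion score on the same instrument, such as some of those included before the questionnaire was switched, drop out of the adjusted comparison. The article does not give their number, which should be reported.
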